### Study design

2.1

The Ace Pilot (Pilot 3) is a randomised, open-label, two-year clinical trial comparing outcomes between an active group receiving a structured cognitive and functional stimulation program and a control group receiving standard care. In parallel, retrospective datasets from Ace's existing cohorts, including clinical, neuropsychological, genetic, CSF and plasma biomarkers, and MRI data, will be shared with the consortium to support the development and validation of the VHP's AI algorithms.

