#### Translational objectives

2.2.2

Patient well-being and intervention impact: To examine the intervention's effects on participants’ physical, psychological, social, and functional well-being, providing a holistic understanding of health, lifestyle, and care needs.Biological and cognitive interactions: To investigate the relationship between biological markers, including genetic profiles, CSF and plasma biomarkers, and MRI measures, and cognitive decline, and to identify the conditions under which e-health interventions are most effective. Plasma biomarkers will be measured at baseline, year 1, and year 2 to track longitudinal changes.Spontaneous speech analysis: To employ automated speech processing for analysing spontaneous speech as a remote and scalable proxy for cognitive status, complementing traditional neuropsychological assessments (23, 24).AI platform development: To contribute to the generation of multidimensional datasets that integrate clinical, biological, cognitive, and patient-reported outcomes in order to refine and validate the VHP's AI models, and to characterize the intervention's efficacy across diverse metrics for the benefit of participants and caregivers.

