### Study participants

2.3

The study participants for the Ace Pilot will consist of 100 individuals aged 60–85, divided into two groups of 50 participants each (active and control groups), see Figure 1. Eligible participants will be diagnosed with MCI according to Petersen criteria (13, 28) with a Clinical Dementia Rating (CDR) score of 0.5 (29) or mild AD dementia as defined by the National Institute on Aging-Alzheimer's Association (NIA-AA) criteria (30) with a CDR score of 1 (29).

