**Figure 1 F1:**

Study design and participant flow for pilot 3 at Ace.

Participants will follow a standardised protocol, with a consensus diagnosis determined by the research team based on a comprehensive evaluation, including neurological, neuropsychological, and social assessments (31). Additionally, participants must show proficiency in using digital devices such as mobile apps, tablets, or computers, as these tools are essential for both the intervention and monitoring processes.

The sample size was defined based on feasibility considerations, reflecting the expected number of eligible individuals who can be recruited during the study period. This estimate considers the typical annual flow of newly assessed patients who undergo the full diagnostic protocol, including neuropsychological evaluation, CSF and MRI, and who are able to attend regular on-site sessions at the centre. As a result, the target of 100 participants represents a realistic and achievable recruitment goal within the operational context of the Memory Unit.

In accordance with Spain's Data Protection Law (Organic Law 3/2018), all participants were informed by a neurologist about the study's goals and procedures before signing an informed consent form. Patient privacy and data confidentiality were safeguarded in compliance with applicable regulations.

Exclusion criteria include a history of medical conditions that could confound cognitive assessments or hinder participation, such as traumatic brain injury, severe depression, stroke, or brain tumors. Participants with significant uncorrected visual or auditory abnormalities, those without access to a digital device or internet connection, and individuals unable to attend regular in-person sessions at Ace will also be excluded.

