### Scheduled visits and assessments

2.4

Participants will be prospectively recruited at Ace's Memory Unit. The majority of patients in this unit are beneficiaries of the Catalan public health system and are typically referred by their general practitioners. Both the active and control groups will follow identical evaluation procedures, as outlined in Table 1, ensuring consistency and comparability in data collection and assessment across the study population.

**Table 1 T1:** Overview of scheduled visits and assessments in pilot 3.

Evaluation/sample		Pre-intervention	Follow-up year 1	Follow-up year 2
Neurology		✓	✓	✓
Neuropsychology		✓	✓	✓
Nursing		✓	✓	✓
Spontaneous speech		✓^a^	✓^a^	✓^a^
MRI		✓	✕	✕
Fluid biomarkers	Plasma	✓	✓	✓
	CSF	✓	✕	✕
	Saliva	✓	✕	✕
Genotyping (PRS and *APOE* ɛ4)		✓	✕	✕
Cognitive and functional stimulation activity		✕	✓^b^	✕
Self-reported data		✓	✓	✓

MRI, magnetic resonance imaging; CSF, cerebrospinal fluid; PRS: Polygenic Risk Score.

^a^
Every 3–4 months remotely.

^b^
Weekly during the first year of follow-up, done remotely and in person.

Clinical, neuropsychological, and biological data will be systematically collected throughout the study to provide a comprehensive evaluation of participants’ progress and the intervention's impact. Clinical and neuropsychological assessments will be conducted in a face-to-face setting at the three critical time points: baseline (pre-intervention) and one-year and two-year follow-ups. These assessments will yield essential insights into participants’ cognitive and functional status over time, enabling a detailed analysis of the intervention's efficacy. Additionally, self-reported data will be gathered via standardised questionnaires during participants’ regular visits as part of the intervention activities. These face-to-face sessions will be carried out during the first year of the project, allowing consistent monitoring of clinical conditions, neuropsychological performances, and subjective experiences, such as quality of life and activity levels. The second-year follow-up is designed to extend the monitoring period and assess the sustainability of the intervention's effects after its conclusion, providing relevant insights into medium-term outcomes. At this final stage, the same clinical, neuropsychological, and self-reported measures are reassessed.

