
The active group will complete the cognitive and functional stimulation intervention at the one-year follow-up. In parallel, the control group will follow the same assessment protocol as the active group, ensuring consistency and comparability in the assessment process. However, participants in the control group will not participate in the stimulation activities provided through the digital platforms developed by the project.

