### Analysis plan

2.7

The primary objective of Pilot 3 is to compare cognitive decline between the active and control groups after a two-year follow-up period. The neuropsychological structure underlying the primary outcome has been previously defined and validated by an expert panel of neuropsychologists (26, 27). Based on this structure, five composite scores will be derived using Structural Equation Modelling, following the methodology described in (23). To evaluate the impact of the intervention across two conditions on these neuropsychological composites, mixed models will be employed. These models will include three time points (baseline, one-year follow-up and two-year follow-up) and will also be applied to secondary outcome measures, such as quality of life, physical activity, and satisfaction with the intervention. Alterations in plasma biomarkers, including pTau181 and pTau217, will adhere to the same analytical framework, allowing for a comprehensive evaluation of both cognitive and biological markers.

In addition, the study will explore modulating effects, such as biological factors (AD-related biomarkers in CSF, PRS, *APOE*, MRI parameters, plasma biomarkers, comorbidities, and medication use) through interaction analyses within the mixed models. Associations between spontaneous speech measures, neuropsychological composites, and plasma biomarkers will be examined using regression models and advanced machine learning techniques. This aspect of the study aims to identify the most predictive parameters of pre- and post-intervention slopes across the five neuropsychological composites. By leveraging these predictive models, the study seeks to advance the understanding of how specific variables contribute to cognitive decline and its modulation, ultimately informing precision medicine approaches for dementia care.

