Building upon this analytical framework, a comprehensive ML approach will be integrated to enhance predictive modelling and improve the understanding of cognitive decline in response to intervention. In contrast to earlier work that relied primarily on shallow or ensemble learning methods applied to acoustic features, the present study will evaluate a broader range of modelling strategies. Acoustic, prosodic, and temporal speech features will be analysed alongside linguistic features derived from automatic transcription, including lexical, semantic, syntactic, fluency-related, and sentiment-related measures (57). Deep-learning architectures—such as convolutional neural networks and autoencoder-based models—will be explored for both acoustic representations and linguistic embeddings. The potential use of large language models (LLMs) will also be examined to extract contextual and semantic information from transcripts (58).

To manage the complexity of high-dimensional data, feature engineering and dimensionality reduction techniques will be applied. Specifically, wrapper-based feature selection methods and autoencoders will be tested to extract the most relevant predictors while minimizing redundancy and noise. A regression-based predictive framework will be used to evaluate the contribution of cognitive, biological, and speech-derived parameters, incorporating ensemble methods such as Random Forests and Gradient Boosting.

To improve model interpretability, explainable AI techniques, such as SHapley Additive exPlanations (SHAP) (59), will be employed to identify the key factors driving cognitive outcomes. Furthermore, longitudinal analyses will be conducted to track cognitive changes over time, enabling an assessment of individual responses to interventions and facilitating the early identification of cognitive decline. This machine learning-driven approach is expected to complement traditional statistical methods, enhancing both the accuracy and interpretability of predictive models in the context of dementia research.

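### Tracking change in a parallel-group trial with one treatment period describes individual trajectories, not individual responses; claims about who benefits should rest on randomised contrasts only

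*Protocol article*

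**What the plan says.** Section 2.7 of the protocol article ends its machine-learning plan by saying that longitudinal analyses will follow cognitive change over time, "enabling an assessment of individual responses to interventions". Earlier in the same section, the predictive models are aimed at the slopes of the five NBACE composites. They are said to advance "understanding of how specific variables contribute to cognitive decline and its modulation, ultimately informing precision medicine approaches for dementia care". The SHAP step is aimed at factors behind cognitive outcomes. The machine-learning work as a whole is presented as clarifying how decline responds to the intervention.

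The design facts that bear on this are:

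- Section 2.1 gives the design: "randomised, open-label, two-year clinical trial comparing outcomes between an active group receiving a structured cognitive and functional stimulation program and a control group". Controls have their usual care.
- Section 2.3 plans 50 participants per arm and states: "The sample size was defined based on feasibility considerations".
- Section 2.6 gives the active arm one treatment period: "The active group will complete the cognitive and functional stimulation intervention at the one-year follow-up". Controls do not take part in the stimulation activities.
- Section 2.4 sets the clinical and neuropsychological assessments at "baseline (pre-intervention) and one-year and two-year follow-ups", with year 2 as follow-up after the intervention has ended. Speech is recorded remotely every 3 to 4 months.
- Section 2.7 also plans interactions between possible effect modifiers and the intervention within the mixed models.

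**The concern.** A participant's response is the difference between the outcome with the intervention and the outcome the same person would have had without it. In this trial each person shows only one of the two. Randomisation identifies the average difference between arms, and average differences within subgroups. It does not identify the difference for one person. Repeated treatment periods or a crossover could help to separate response from natural course and error, but none is described.

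The predictive step adds to the problem. A model that predicts slope or outcome finds variables that go with faster or slower decline. Variables such as APOE status, plasma pTau217 or diagnosis may predict decline strongly in both arms without changing the effect of the intervention. As written, the predictive step names no between-arm contrast, yet its findings are meant to inform precision medicine. At stake is the claim about who benefits: prognostic markers could be taken for markers of benefit even if the intervention had no effect, or the same effect in everyone.

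**Working it through.** The protocol states no figure for this claim and no power calculation, so there is nothing to reproduce beyond 2 x 50 = 100. From the documents: two parallel arms of 50, one treatment period, and three NBACE assessments per person. All means, SDs and effects below are assumptions, in composite SD units.

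**Identification.** For an active participant, change = natural course + practice + response + (follow-up error - baseline error). For a control, the same without response. Only one sum is observed per person. Denser speech sampling shrinks the error term for speech but supplies no untreated comparator for the same person.

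**1. No effect for anyone.** With mean change m and SD of change s, P(change >= 0) = Phi(m/s):
- m = -0.3, s = 0.6: Phi(-0.50) = 0.31
- m = -0.3, s = 0.8: Phi(-0.375) = 0.35
- m = -0.5, s = 0.6: Phi(-0.83) = 0.20
- m = -0.5, s = 0.8: Phi(-0.625) = 0.27

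So 20% to 35% of participants, in either arm, show no decline.

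**2. The same effect for everyone.** Take mean natural change -0.3, natural-course SD 0.3 to 0.5 and error SD per visit 0.3 to 0.5. The variance of change runs from 0.3² + 2 x 0.3² = 0.27 to 0.5² + 2 x 0.5² = 0.75. With an identical effect of +0.2, no decline is seen in Phi(-0.1/√0.27) = 42% to Phi(-0.1/√0.75) = 45% of active participants. In controls it is seen in Phi(-0.3/√0.27) = 28% to Phi(-0.3/√0.75) = 36%. Some active participants look like responders and others do not, although response does not vary at all.

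**3. Response truly varies, SD 0.2, independent of natural course.** The correlation between observed change and true response is 0.2/√(variance of change + 0.04). This is 0.2/√0.31 = 0.36 at best and 0.2/√0.79 = 0.22 at worst.

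**4. What the spread of change can show at group level.** With equal true variances, the ratio of change variances at 50 per arm has a 95% range of 0.57 to 1.76 (F with 49 and 49 degrees of freedom). As an SD ratio this is √0.567 = 0.75 to √1.762 = 1.33. A response SD of 0.2 raises the true variance ratio only to between 0.79/0.75 = 1.05 and 0.31/0.27 = 1.15, with power of 5% to 8%. Power of 80% needs a ratio of about 2.24, that is, a response SD of √(2.24 - 1) = 1.1 times the control SD of change.

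**5. What the interactions can show.** For a balanced binary modifier the standard error of the interaction is 4/√100 = 0.4 SD. A difference in effect of 0.5 SD then has power Phi(0.5/0.4 - 1.96) = Phi(-0.71) = 24% at two-sided 0.05. The contrast is valid but imprecise.

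**The case against.** The strongest reply is that this is one loose phrase. Read with the words about following change over time, it can mean observed trajectories, and section 2.6 elsewhere speaks of predicting individual health trajectories. The protocol defines no responder, sets no response threshold and promises no individual effect estimate. It already plans modifier interactions in the two-arm mixed models, which are the natural vehicle for the objective in section 2.2.2 "to identify the conditions under which e-health interventions are most effective". The analysis is exploratory.

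Most of this stands. The section 2.2.2 objective is not in error, since subgroup contrasts can address it, and neither is the visit schedule. The SHAP sentence and the individual-response sentence are separate, and nothing says that SHAP rankings will be read as response. The article does not say whether arm enters the machine-learning models. That detail may sit in a fuller document, and its absence here is no fault. The three-visit count applies to NBACE, not to speech.

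A reader might go further and infer that prognosis will be reported as response, or that slow progressors will be labelled responders and their biomarkers built into the VHP as selection rules. The documents do not support that. Section 2.6 says that algorithms will propose tailored interventions, but it describes no rule derived from change in treated participants.

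The reply does not remove the positive statement that tracking change makes individual response assessable. Nor does it remove the gap between models aimed at slopes and outcomes and a description of them in terms of response to the intervention.

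**Conclusion.** The point holds in this limited form. The design identifies average and subgroup effects, not individual responses, and the wording in section 2.7 claims the latter. Predictors of slope or outcome are prognostic and risk being read as predictors of response. The primary comparison and the planned mixed-model interactions are unaffected.

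The size can only be illustrated. The 20% to 35% without decline under no effect rests on assumed means and SDs and on a cut-off of change at or above zero that the protocol does not use. The correlation of 0.22 to 0.36 rests on an assumed response SD of 0.2, independent of natural course. The SD-ratio range of 0.75 to 1.33 needs only 50 analysed per arm, equal true spread and roughly normal changes. The identification argument itself needs none of these values.

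**What to change.** In section 2.7 and in the analysis plan:

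1. Write of individual trajectories where the text now speaks of individual responses to interventions.
2. Label predictors of change from the machine-learning and SHAP steps as prognostic.
3. Base any statement about who benefits on randomised contrasts only. These are the arm-by-time-by-modifier terms in the planned mixed models or, if machine learning is used for this purpose, models fitted on both arms with arm as an input and reported as predicted change under active minus predicted change under control. No particular algorithm is needed; a causal forest is not required.
4. Show any responder proportion, and the SD of change, for both arms side by side.

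This costs a change of wording and modest extra analysis of data already being collected. The drawback is that estimates of differential benefit will be far less precise than predicted trajectories at 50 per arm, and should be presented as such.

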## Discussion

3

The COMFORTage project exemplifies a transformative and multidisciplinary effort to advance dementia care through the integration of cutting-edge digital technologies, biomarker-based research, and precision medicine strategies. By bringing together a consortium of 39 organizations across 12 countries, this initiative utilises a wide range of expertise and resources, ensuring scalability and external validity of its findings across various healthcare systems.

One of the project's distinguishing features lies in its advanced technological infrastructure. The VHP integrates multidimensional health data, encompassing all key aspects of patient information, supported by the incorporation of PDTs to enhance precision and personalization (60). These strategies enable adaptive decision-making, optimize interventions in real-time, and provide a secure, scalable framework for patient-centred care. Features such as explainable AI, gamified interventions, and educational components further improve engagement and usability (61, 62).

Although the COMFORTage project addresses a wide range of age-related conditions and populations, Pilot 3, led by Ace, focuses specifically on individuals with MCI and mild AD dementia. This pilot assesses the effectiveness of tailored cognitive and functional stimulation interventions, aiming to enhance patient outcomes and inform scalable care strategies. Through a randomised, open-label trial design, participants are divided into active intervention and control groups to rigorously assess outcomes.

By combining retrospective datasets—including thousands of clinical, neuropsychological, genetic, and imaging records—with prospective longitudinal assessments, Pilot 3 will generate a rich dataset for predictive modelling. These assessments incorporate both traditional biomarkers, such as plasma and MRI, and non-invasive biomarkers, including spontaneous speech analysis, which detects subtle cognitive changes through linguistic parameters such as lexical fluency and syntactic complexity (23, 63). Additionally, genetic variables such as PRS and the presence of the *APOE ε*4 allele are included, further enriching the dataset and enhancing its predictive capabilities (43).

Findings for Pilot 3 are contextualised within the broader COMFORTage framework, which encompasses complementary pilots addressing other aspects of age-related health challenges. These include systemic approaches to care delivery, physical health and mobility, and prevention strategies targeting broader ageing populations. Together, these efforts refine precision medicine approaches, ensuring interventions are not only effective but also scalable and adaptable to various healthcare systems and patient demographics (64, 65). Although the Ace dataset will include 100 participants, its contribution gains substantial relevance when combined with the broader multimodal datasets generated across the COMFORTage consortium. These larger and more diverse cohorts provide a powerful framework for validating AI-driven models and for situating the Ace data within a wider European context. Importantly, the consortium-wide datasets complement established public cohorts—such as ADNI and OASIS (66, 67)—by contributing real-world clinical information, fluid biomarkers, spontaneous speech recordings, and digital-platform activity collected within community-based intervention settings.

Studies suggest that multimodal stimulation programs combining cognitive, social, and digital activities may stabilise or modestly enhance cognitive trajectories in individuals with MCI and early AD, particularly in executive and attentional domains (68, 69). Likewise, plasma biomarkers show strong associations with longitudinal cognitive decline and may be expected to correlate with neuropsychological slopes (70). MRI-based measures have also demonstrated additive predictive value when integrated with neuropsychological data (71). Given these trends, we anticipate that the multimodal dataset generated in Pilot 3 will support more accurate, personalised prediction models within the VHP.

Despite its innovative and comprehensive design, the COMFORTage project faces several key challenges that may influence its overall impact and scalability (72). Among these, the digital divide remains a significant concern, particularly in terms of unequal access to technology and varying levels of digital literacy among older adults. To mitigate this risk, structured onboarding sessions and guided pre-training may be used to help participants become familiar with digital platforms, reducing early practice effects and enhancing long-term engagement.

Likewise, regional differences in healthcare infrastructure and resource availability may affect the feasibility of implementing standardised digital platforms at scale. Another important consideration involves ethical and legal aspects related to the management of sensitive data, especially when dealing with genetic information and biomarker profiles. Ensuring data privacy, patient consent, and compliance with regulatory frameworks like GDPR is crucial to maintain public trust and protect participants’ rights.

From a methodological perspective, Pilot 3 incorporates several overlapping digital interventions—such as Healthentia, Eligence, and the Linguistic Games tools—that deliver cognitive stimulation, functional training, and patient monitoring. Although this multimodal approach enhances the realism and relevance of the intervention, it also poses analytical challenges: it is difficult to disentangle the specific contribution of each platform to the observed outcomes. Improvements in cognitive function or quality of life may stem from the synergistic effects of multiple factors, including physical activity, digital engagement, social interaction, and cognitive challenge.

This limitation is intrinsic to many complex, integrative interventions and reflects the multifactorial nature of neurodegenerative conditions. While the study does not allow for precise attribution of effects to single components, it aligns with the project's overarching goal: to promote holistic, patient-centred care through scalable, real-world strategies. Importantly, the availability of extensive clinical, demographic, and biological data enables us to account for alternative explanations and rule out several potential confounders when interpreting the observed effects. Future research may benefit from experimental designs such as factorial or dismantling trials to further isolate and quantify the contributions of individual intervention elements within broader care models.

In conclusion, while COMFORTage addresses a diverse array of age-related health challenges, Pilot 3's emphasis on cognitive and functional stimulation interventions, supported by advanced biomarker analyses, speech-derived metrics, and digital health tools, is expected to make a significant contribution to the project's overarching goals. By integrating multimodal data within a precision-medicine framework, this pilot is well positioned to inform scalable, evidence-based strategies for early intervention in cognitive decline. Collectively, the interconnected pilots offer a cohesive foundation for future innovation in dementia care, supporting real-world implementation across diverse populations and healthcare settings.
